## Methods I: Participants, interventions, and outcomes

### Study design

This is a single-center, evaluator-masked, non-inferiority, cross-over Randomized Controlled Trial (RCT). This study is approved by the Ethical Cantonal Board of Geneva, Switzerland (CCER N° 2021-D0090) and all methods are performed in accordance with the relevant guidelines and regulations. The protocol for this study was designed according to the SPIRIT (Standard Protocol Elements: Recommendations for Interventional Trials) 2013 Statement [35, 36]. Recruitment of participants is planned from May 2022 to December 2024. The trial will take place in the Department of Ophthalmology of the Geneva University Hospitals (Switzerland). The amblyopic cohort will take part in the cross-over design. They will be randomly assigned to take part either first in the study-intervention arm and second in the control-treatment arm, or vice versa (AB or BA), stratified according to the type of amblyopia (anisometropic, strabismic or mixed). They are not masked to the order of the received training. The age-matched control cohort will only complete the VR-based intervention.

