This study protocol describes the setup for a Randomized Controlled Trial (RCT) comparing the effects of a personalized, VR, and home-based binocular stimulation intervention in people with residual amblyopia compared to standard care and to healthy controls. The first objective is to examine whether VR game-based interventions are not inferior to refractive correction in residual amblyopia and whether it will result in similar or better retention of the improvements. Secondly, we aim to explore whether such VR-derived improvements in the amblyopic cohort are beyond the changes we find in the control cohort. Lastly, we will study the underlying neural mechanisms of improvements by measuring brain activity and will ascertain whether such mechanisms can predict, in combination with clinical measures, treatment outcome.

This RCT will address the following research aims:a) test the efficacy of a serious game-based binocular stimulation in a VR environment in improving Best Corrected Visual Acuity (BCVA), compared to refractive correction in individuals with residual amblyopiab) test the potential VR-based benefits on clinical measures of other vision skills like stereoacuity, functional vision (i.e., reading skills), and suppression, compared to refractive correction in individuals with residual amblyopiac) test the potential benefits of VR-based training on visual and audiovisual selective attention and motor control skills, compared to refractive correction and to the control groupd) evaluate the adherence and safety of the VR-based intervention compared to standard caree) test the potential VR-based benefits on eye-related quality of lifef) test the potential VR-based benefits on cortical responses including visual, higher cognitive processes of audio-visual, and motor control skills in both cohortsg) test whether the potential VR-derived benefits on vision, attention and motor control skills in residual amblyopic patients are larger from those found in the control cohorth) identify clinical and electrophysiological factors predicting treatment response in individuals with residual amblyopia.

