### Participants and eligibility criteria

The study population will include 30 individuals with residual amblyopia (strabismus, anisometropic and mixed types) and 30 age-matched normally sighted individuals between 6–35 years old, as younger children seem to have difficulties in understanding the games [37]. General exclusion criteria are the presence of (i) auditory deficits or loss, (ii) uncorrected visual disorder, (iii) coexistence of ocular or neurological disease, and (iv) developmental, psychological, or sensorimotor disorder. Additional inclusion criteria for the amblyopic cohort are: (i) residual amblyopia defined as BCVA of < 20/20 in the amblyopic eye and an interocular difference of ≥ 2 lines persisting even after refractive correction; (ii) stable BCVA for at least 2 consecutive measurements over 6 months. Additional exclusion criteria for the amblyopic cohort are: (i) untreated or newly diagnosed anisometric, strabismic or combined amblyopia, i.e., a BCVA interocular difference of ≥ 2 lines that is untreated or newly diagnosed; (ii) atropine treatment currently or 3 months prior to enrolment in the study; (iii) eye surgery except those to correct strabismus; (iv) strabismus over 20D or with large eccentric fixation. In this study, as we include both healthy and amblyopic cohorts, we will use the terms dominant and non-dominant eye to refer also to the fellow and amblyopic eye, respectively.

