### Interventions

#### Experimental intervention for the amblyopic cohort

The experimental intervention consists of playing eight stereoscopic serious games using the Vivid Vision Home software (Vivid Vision Inc., San Francisco, CA, USA), embedded in a VR headset. After a training session at the Dept. of Ophthalmology, the intervention is conducted at home, at the participant’s and family’s convenience. Participants’ success in the games depends on the integration of information from the amblyopic and the fellow eye, as the games are designed to improve binocularity. The games are aimed at training anti-suppression/fusion (Hoopie, Ring Runner, Breaker, Pepper Picker), stereopsis (Bubbles, Bullseye), and visual processing (Flash Match). Such game variability will improve the compliance among the older participants [37]. The prescribed dosage for game playing is 30 min per day, 5 days per week, over 8 weeks, with a total game time of 20 h. To prevent participants from playing more than 30 min per day, the software is programed to block access to its games until the next day. Participants can split the prescribed dosage of 30 min per day into smaller sessions, if they desire to do so. All participants will be instructed to wear their glasses with the updated refractive correction while they play the VR-based games.

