### Sample size

We calculated the sample size necessary to obtain a significant difference (α = 0.05) between our treatment and refractive correction based on medium effect size (F’s Cohen = 0.25) with 80% power for a crossover design immediately after the intervention on our primary endpoint. This estimation resulted in a total sample of 24 individuals with residual amblyopia. To account for the potential dropout, we will increase the sample size by 25%, resulting in 30 individuals with amblyopia. We will additionally recruit 30 age-matched typically developing individuals to undergo the serious game VR-training. This sample will serve to account for the potential changes in vision, selective attention and motor control which are known to occur in healthy adults after a VR-training.

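### The design and first objective are framed as non-inferiority to glasses, but aim (a) and the sample size are for a difference, so the same null result could be reported as success or as failure

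*Protocol article*

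**What the plan says.** Two places in the protocol article frame the trial as non-inferiority. Study design: "This is a single-center, evaluator-masked, non-inferiority, cross-over Randomized Controlled Trial (RCT"). Background, objectives: "The first objective is to examine whether VR game-based interventions are not inferior to refractive correction in residual amblyopia". The second half of that objective concerns retention of the improvements, worded as similar or better.

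Two places frame it as a test for a difference. Aim (a), in the same Background section, is to "test the efficacy of a serious game-based binocular stimulation in a VR environment in improving Best Corrected Visual Acuity (BCVA), compared to refractive correction". Sample size: "We calculated the sample size necessary to obtain a significant difference (α = 0.05) between our treatment and refractive correction", with Cohen's f = 0.25, 80% power and the comparison made immediately after the intervention on the primary endpoint. This gives 24, raised by 25% to 30.

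Three further statements bear on what the comparator can show:
- Eligibility requires an interocular difference of at least 2 lines that remains after refractive correction, and "stable BCVA for at least 2 consecutive measurements over 6 months". Untreated or newly diagnosed amblyopia is excluded.
- The control treatment is 8 weeks of wearing the prescribed glasses.
- In the VR period, participants are told to "wear their glasses with the updated refractive correction while they play the VR-based games".

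**The concern.** A non-inferiority claim and a superiority claim rest on different null hypotheses. If VR and glasses end up the same, a non-inferiority trial can call that success, while a superiority trial must call it a failure to show benefit. The text shown supports both readings, and nothing in it says which one decides the trial. The hypothesis could therefore be chosen after the results are known.

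Non-inferiority is normally used when the comparator has a benefit that the new treatment should preserve. Here the comparator is the correction on which patients have already stabilised with a residual deficit. Little further change on it is to be expected, so there is little benefit to preserve. Not being inferior to it would not show that the games treat residual amblyopia, which is the question in aim (a) and the one the Discussion needs answered to decide whether to pursue or abandon the approach.

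**Working it through.** **1. Which hypothesis does the figure of 24 belong to?**

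Inputs from Sample size: f = 0.25, α = 0.05, power 80%. Sidedness, the number of measurements m and the within-patient correlation ρ are not stated, so m and ρ are assumed below. The F test is two-sided in effect.

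Repeated-measures power uses a noncentral F with λ = f² · N · m / (1 − ρ), and degrees of freedom m − 1 and (N − 1)(m − 1).

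- m = 4, ρ = 0.5, N = 24: λ = 0.0625 × 24 × 4 / 0.5 = 12.0, df 3 and 69, power 0.817. At N = 23 power is 0.797, so 24 is the smallest N.
- m = 2, ρ = 0.65, N = 24: λ = 0.0625 × 24 × 2 / 0.35 = 8.57, df 1 and 23, power 0.801. This is a paired t-test with standardised difference dz = √(8.57/24) = 0.598.
- m = 2, ρ = 0.5: the smallest N is 34.

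The stated 24 is therefore reproduced under plausible assumed values, each time as a test for a difference. No margin enters the calculation.

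**2. How often would a programme with no effect be declared non-inferior?**

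Assumptions, because the article gives neither a margin nor an SD: margin M in logMAR, SD of the within-patient difference in BCVA, n = 24 completers, true difference 0, one-sided α = 0.025.

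P(declare non-inferior) = P(T > 2.069), where T is noncentral t with 23 df and noncentrality (M / SD) × √24, and √24 = 4.899.

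| M | SD | Noncentrality | Probability |
|---|---|---|---|
| 0.10 | 0.10 | 1.000 × 4.899 = 4.899 | 0.997 |
| 0.10 | 0.15 | 0.667 × 4.899 = 3.266 | 0.878 |
| 0.05 | 0.10 | 0.500 × 4.899 = 2.449 | 0.650 |
| 0.05 | 0.15 | 0.333 × 4.899 = 1.633 | 0.346 |
| 0.05 | 0.20 | 0.250 × 4.899 = 1.225 | 0.216 |

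A reference point that needs no logMAR values: if the margin equalled the paired effect detectable with 80% power at n = 24 (dz = 0.597), a programme with no effect would pass 80% of the time.

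**3. The like-for-like comparison.** A two-sided 5% superiority test on the same null programme is significant in 5% of trials, half in each direction. A false claim that VR is better therefore occurs in 5% / 2 = 2.5%.

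**4. What a non-inferiority trial would need.** With a one-sided 2.5% test, 80% power and true difference 0, a margin of 0.05 needs 34 patients at SD 0.10 and 73 at SD 0.15. A margin of 0.10 needs 10 and 20. Whether 24 is too few, adequate or more than enough therefore depends entirely on values that the article does not give.

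**The case against.** The operative plan can be read as a difference test that carries a conflicting label. The abstract speaks of efficacy and effect and never of non-inferiority, and the sample size powers a difference on the primary endpoint. A linear mixed model yields a treatment contrast with a confidence interval that can serve either reading, so the stated analysis is not itself at fault. This stands, and it limits the point in four ways.

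- A reader might infer that efficacy would go untested. The document does not support that: aim (a) asks the efficacy question and Sample size powers it. The defect is that two competing claims are both on offer.
- A reader might infer that a useless programme is bound to be declared non-inferior. The probability depends on a margin and an SD that are not given. It runs from near certainty to about one in three over the main assumed range, and to 0.22 at margin 0.05 with SD 0.20. Only the word could is supportable.
- A reader might treat the absence of a margin as an error in its own right. A condensed article may leave the margin to the full protocol or SAP. A margin stated elsewhere would still not turn the published difference-based calculation into a non-inferiority calculation.
- Two premises are inferences. The article requires glasses during play and is silent on the rest of the VR period. It also refers to updated correction, so a new prescription might shift acuity, and it gives no tolerance for what counts as stable. Neither uncertainty would make a non-inferiority result evidence that VR improves vision.

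**Conclusion.** The point holds as a contradiction within the text shown: Study design and the first objective say non-inferiority, while aim (a) and Sample size say difference. It should be resolved before analysis, because it decides whether a null result counts as success. With 24 completers and the assumed margins (0.05 to 0.10 logMAR) and SDs (0.10 to 0.15), a programme with no effect could be declared non-inferior with probability 0.35 to 0.997, against 2.5% for a false claim of benefit under superiority. Even the lowest of these is more than ten times 2.5% (0.346 / 0.025 = 13.8). The size rests on the assumed values. The contradiction does not.

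**What to change.** In Study design and in the first objective, replace the non-inferiority wording with one primary hypothesis: VR with glasses is superior to glasses alone on amblyopic-eye BCVA immediately after treatment, tested two-sided at 5%. This matches aim (a) and the existing sample size. State that non-inferiority will not be used as a fall-back claim of efficacy. It would also help to give the correlation and the number of measurements behind the 24.

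The cost is an amendment to the protocol and registry entry. Recruitment was planned from May 2022, so the trial may already be enrolling, and changing a first objective then is more than an editorial correction. No extra patients or visits are needed. The conclusion becomes harder to claim.

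If the sponsor prefers to keep non-inferiority, it must justify a margin, explain what benefit of continued glasses that margin protects, and base the sample-size statement on it.

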### Participants and eligibility criteria

The study population will include 30 individuals with residual amblyopia (strabismus, anisometropic and mixed types) and 30 age-matched normally sighted individuals between 6–35 years old, as younger children seem to have difficulties in understanding the games [37]. General exclusion criteria are the presence of (i) auditory deficits or loss, (ii) uncorrected visual disorder, (iii) coexistence of ocular or neurological disease, and (iv) developmental, psychological, or sensorimotor disorder. Additional inclusion criteria for the amblyopic cohort are: (i) residual amblyopia defined as BCVA of < 20/20 in the amblyopic eye and an interocular difference of ≥ 2 lines persisting even after refractive correction; (ii) stable BCVA for at least 2 consecutive measurements over 6 months. Additional exclusion criteria for the amblyopic cohort are: (i) untreated or newly diagnosed anisometric, strabismic or combined amblyopia, i.e., a BCVA interocular difference of ≥ 2 lines that is untreated or newly diagnosed; (ii) atropine treatment currently or 3 months prior to enrolment in the study; (iii) eye surgery except those to correct strabismus; (iv) strabismus over 20D or with large eccentric fixation. In this study, as we include both healthy and amblyopic cohorts, we will use the terms dominant and non-dominant eye to refer also to the fellow and amblyopic eye, respectively.

### Interventions

#### Experimental intervention for the amblyopic cohort

The experimental intervention consists of playing eight stereoscopic serious games using the Vivid Vision Home software (Vivid Vision Inc., San Francisco, CA, USA), embedded in a VR headset. After a training session at the Dept. of Ophthalmology, the intervention is conducted at home, at the participant’s and family’s convenience. Participants’ success in the games depends on the integration of information from the amblyopic and the fellow eye, as the games are designed to improve binocularity. The games are aimed at training anti-suppression/fusion (Hoopie, Ring Runner, Breaker, Pepper Picker), stereopsis (Bubbles, Bullseye), and visual processing (Flash Match). Such game variability will improve the compliance among the older participants [37]. The prescribed dosage for game playing is 30 min per day, 5 days per week, over 8 weeks, with a total game time of 20 h. To prevent participants from playing more than 30 min per day, the software is programed to block access to its games until the next day. Participants can split the prescribed dosage of 30 min per day into smaller sessions, if they desire to do so. All participants will be instructed to wear their glasses with the updated refractive correction while they play the VR-based games.

At the beginning of the training, the visual contrast of objects visible to the fellow eye is decreased relative to the amblyopic eye. Each week and according to the participant’s performance, the difference in the input strength between the eyes will become smaller. The goal is to no longer need any modification of images’ features to combine them, and to perceive depth all the time. The difficulty of the games will be automatically adjusted based on an algorithm developed by Vivid Vision Inc. and integrated in the software (Smart Assist). This automatic adjustment aims at individualizing the treatment to meet the therapeutic needs of the patient. By individualizing the treatment to the patient’s needs, we hope to improve the efficacy of the treatment. To this purpose, built-in tests in the Vivid Vision Home software (Prism Tuner—to optimize the virtual prism settings for a patient’s treatment session, Stereoacuity – to estimate of the patient’s stereoscopic vision) will be performed systematically to increase or decrease the amount contrast needed for the patient to successfully play. These changes aim to keep the games challenging to the current level of visual skills of the participants. This “adaptiveness” of the games’ difficulty levels is meant to keep participants engaged and to support their improvement over the course of the whole training. Additionally, after each training session, participants or participants’ parents will report in a gaming diary, which they have been given by the experimenters, duration of their gaming session that day, their feelings about it (i.e., experiencing fun or, alternatively, difficulty during the game) as well as any adverse event (i.e., nausea, headache, diplopia). Participants will be instructed to inform the research team as soon as they experience any adverse event. Through the web-based dashboard of Vivid Vision Home, the research team will be able to see the participant’s activities, follow up on the prescribed play time and will get a notification after 2 days have passed without playing.

#### Control intervention for the amblyopic cohort

The control treatment for the amblyopic cohort involves wearing the prescribed glasses with the necessary refractive correction, which is the standard treatment for individuals who have undergone the patching treatment and been diagnosed with residual amblyopia. Participants will wear their glasses for the same duration as the experimental intervention (i.e., 8 weeks). The participants are expected to not receive any concomitant care or any additional interventions.

#### Control intervention for the control cohort

The control cohort will only undergo the VR-based intervention with the stereoscopic serious games on the Vivid Vision Home software. However, the games will not have any between-eyes image difference in terms of contrast (although those games with dichoptic stimulation will be displayed in the same way). The Smart Assist algorithm will be turned off for this cohort.

### Outcomes

Our primary outcome is best corrected visual acuity. Among our secondary outcomes are stereoacuity, functional vision (reading), visual cortical responses, higher cognitive processes of multisensory attention (i.e., visual and audiovisual attention), motor control skills, and eye-related quality of life. Primary and secondary outcome measures will be evaluated before and after each treatment as well as 8-weeks follow up (a more detailed timeline can be found later in this protocol).

#### Primary outcome

Best Corrected Visual Acuity (BCVA) will be measured using the Sloan chart adapted to age. The BCVA is the diagnostic vision measure for amblyopia (i.e., an interocular difference in visual acuity between the amblyopic and non-amblyopic eye) and it has been shown to improve with patching treatment as well as with novel treatments with binocular stimulation [17, 19, 38]. This will be administered by certified orthoptists who are masked to the treatment order.

#### Secondary outcomes I: clinical measures

##### Binocular vision: stereoacuity

Stereoacuity refers to the smallest detectable depth difference that can be seen in binocular vision. When binocular vision is present, the binocular function is the best stereoscopic acuity, measured in arc seconds. The presence of binocular vision will be first tested with the Bagolini. Stereoacuity will be measured with the Lang stereotest II, the TNO stereo test, and Titmus tests at every assessment point and the assessors are masked to treatment order.

Additionally, we will measure stereoacuity with a novel, 3D tablet-based test called ASTEROID [39] at every assessment point and the assessors are not masked to treatment order, as this is computerized test.

##### Binocular vision: interocular misalignment

Interocular misalignment refers to the degree to which two eyes' axes are not parallel. It can be measured with the Prims-cover test. Result of the Prism-cover test of one eye turning upon covering the other indicates eye misalignment. Red filter involves asking patient to fixate on a white circle at the end of the room and placing a red filter on the patient's fellow eye. If the patient reports a red pinkish light, there is binocular fusion. Additionally, it provides information on the alignment of the eyes based on normal retinal correspondence or binocular fusion based on abnormal retinal correspondence (e.g. microstrabismus). The location of the red circle in relation to the white circle lets conclude the nature of the deviation (esotropia, exotropia or vertical deviation). These tests are administered at every assessment point and the assessors are masked to treatment order.

##### Binocular vision: measurements in the Vivid Vision Home software

A Composite Depth Score estimate is measured (0–30) where 0 indicates no stereovision and 30 indicates a stereo threshold of 20 arc sec or better. Patients need to choose which of 4 circular stimuli are floating off the surface, where with each correct response the stimuli become smaller and the disparity decreases. The degree of binocular vision is estimated with a virtual Worth 4 Dot test, revealing normal vision, double vision, or suppression of left or right eye [40]. Ocular posture adjustment estimates the minimal correction needed for patient’s ocular posture in a horizontal, vertical and rotational prism is estimated in prism diopters through a Maddox rod like test [41], where the patient aligns vertical and horizontal lines with a spot or a pair of horizontal lines. Vergence is evaluated through the speed of the patient’s ability to switch between difference vergence demands is estimated in seconds as the participant is aligning a series of shapes or symbols until they make up a single line [42]. Lastly, the vergence range is the participant’s maximal horizontal and/or vertical vergence ability and is estimated in prism diopters as the participant is aligning a series of shapes or symbols until they make up a single line [42]. These tests are measured at every assessment point and are automatically performed by the software.

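### The in-headset binocular scores are secondary outcomes for VR versus glasses, but only the VR period adds practice on that software, so a difference on them may partly reflect familiarity

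*Protocol article*

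**What the plan says.** Under Secondary outcomes I: clinical measures, the section on measurements in the Vivid Vision Home software lists five scores produced by the intervention software:

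- a stereo score: "A Composite Depth Score estimate is measured (0–30) where 0 indicates no stereovision and 30 indicates a stereo threshold of 20 arc sec or better"
- a virtual Worth 4 Dot test
- an ocular posture estimate
- vergence speed
- vergence range: "the vergence range is the participant’s maximal horizontal and/or vertical vergence ability and is estimated in prism diopters"

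The section closes with "These tests are measured at every assessment point and are automatically performed by the software".

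The aims at the end of the Background include one to "test the potential VR-based benefits on clinical measures of other vision skills like stereoacuity", along with reading and suppression, against refractive correction. The Statistical analysis section applies linear mixed models to primary and secondary outcomes, with refractive correction as one comparator.

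The section on the experimental intervention says that built-in tests of the same software "will be performed systematically to increase or decrease the amount contrast needed for the patient to successfully play". Two are named: a Stereoacuity test and "Prism Tuner—to optimize the virtual prism settings for a patient’s treatment session". The control intervention for the amblyopic cohort is glasses alone, with no headset use described between visits.

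**The concern.** The software that delivers the treatment also produces these outcome scores, and parts of its test set are run as part of that treatment. A patient leaving the VR period has spent weeks in the headset and has repeated at least a stereo test in it. A patient leaving the glasses period has met the software only at scheduled assessments (and earlier, if VR came first). A better in-headset score after VR could mean better binocular vision, more skill with the test and device, or both, and the score alone cannot separate them.

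The article gives the tests outside the headset no precedence over the in-headset scores. A positive Composite Depth Score could therefore be reported as a VR benefit even if the independent stereo tests show none. The point is sharpest for suppression, which the aims name: the virtual Worth 4 Dot is the only outcome test that the article describes as reporting suppression.

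**Working it through.** **1. Exposure in each period.** The plan states "The prescribed dosage for game playing is 30 min per day, 5 days per week, over 8 weeks, with a total game time of 20" hours. Check: 5 days × 8 weeks = 40 days, and 40 × 0.5 h = 20 h, which agrees. The glasses period prescribes 0 h in the headset.

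The number of extra test runs is not stated. The text says only that they are systematic. The weekly wording belongs to something else: "Each week and according to the participant’s performance, the difference in the input strength between the eyes will become smaller". As an assumption, weekly runs would give about 8 and runs on every training day would give 40. Either count measures exposure, not bias.

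**2. Which scores are touched, and how firmly.**

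| In-headset outcome | Nearest named training test | What the text supports |
|---|---|---|
| Composite Depth Score | Stereoacuity | Repeated stereo testing documented; not stated to be the identical test |
| Ocular posture | Prism Tuner | Repeated testing plausible; link not stated |
| Vergence speed, vergence range | none | General headset familiarity only |
| Virtual Worth 4 Dot | none | General headset familiarity only |

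**3. What the crossover removes.** Suppose binocular vision does not truly change. Let r1 and r2 be the ordinary retest gains in periods 1 and 2, e the extra gain from VR-period practice, and c the effect of retained VR practice on the glasses result in the VR-first sequence.

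- VR-first, VR minus glasses: (r1 + e) − (r2 + c)
- Glasses-first, VR minus glasses: (r2 + e) − r1
- Average of the two sequences: e − c/2

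Ordinary retest gain cancels. The extra practice e does not, because it goes with the treatment and not with the period or the person.

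The sign of c is not fixed. By the Participant timeline, T3 is both the VR follow-up and the glasses baseline in the VR-first sequence. Retained practice may raise T3. If change from T3 is analysed and the practice then fades, or the score is near its ceiling of 30, c is negative and the apparent VR benefit grows. If post-treatment values are compared, c is positive and the benefit shrinks.

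**4. Illustration of size.** The article gives no practice effect, so every input here except n is an assumption: no true change, c = 0, a VR-only practice gain of d test standard deviations, within-person correlation ρ, and a two-sided 0.05 within-person contrast on n − 2 degrees of freedom. The values of n come from the Sample size section (24 evaluable, 30 recruited).

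Noncentrality = d × √n / √(2(1 − ρ)). For d = 0.3, n = 24, ρ = 0.5 this is 0.3 × 4.899 / 1 = 1.47, and the chance of a significant false VR benefit is 29%.

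| n | ρ | d = 0.1 | d = 0.2 | d = 0.3 | d = 0.5 |
|---|---|---|---|---|---|
| 24 | 0.5 | 7% | 15% | 29% | 65% |
| 24 | 0.7 | 9% | 23% | 44% | 86% |
| 30 | 0.5 | 8% | 18% | 36% | 75% |
| 30 | 0.7 | 10% | 28% | 54% | 93% |

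The nominal rate in that direction is 2.5%. The table shows how sensitive the contrast is to a one-sided practice gain. It does not estimate this trial's bias.

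**The case against.** Four points on the other side have force.

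- **Stereoacuity is measured independently.** Lang II, TNO and Titmus are done by masked assessors, and ASTEROID runs on a tablet. Bagolini, prism-cover and red-filter tests are also masked. Nothing in the article says that the conclusion rests on the headset scores. This stands and limits the harm, but the article does not say that these tests take precedence either.
- **The tests also bracket the glasses period.** A reader might infer that all practice falls on VR. The documents do not support that: the software tests are done at T1 to T5, and in the glasses-first sequence the first retest falls in the glasses period. Only the extra between-visit exposure is one-sided.
- **Not every score is repeated in training.** A reader might infer that the vergence and Worth 4 Dot tests are rehearsed too. They are not among the named training tests. Nor does the article say that familiarity would move ocular posture or a categorical Worth 4 Dot result towards benefit.
- **Ranking secondary outcomes commonly belongs to the statistical analysis plan, which is not shown.** This is true of ranking in general. But the status of these scores as secondary clinical outcomes, and the comparison with refractive correction, are fixed in the article.

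Automatic scoring is no answer, since it removes assessor bias and not practice. The healthy cohort plays the games but has no glasses period, its Smart Assist is off, and its built-in testing is not described, so it does not repair this contrast.

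**Conclusion.** The concern holds in a limited form. On the in-headset scores, a VR-versus-glasses difference may partly reflect test practice or device familiarity. Support is firmest for the stereo score, plausible for ocular posture, and limited to general headset familiarity for vergence and Worth 4 Dot. The crossover cancels ordinary retest gain but not the extra VR-period exposure, and retained practice after VR-first may shift the T3 baseline.

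The size cannot be derived from the document. What is documented is up to 40 days and 20 h of headset use against none, plus an unstated number of built-in test runs. It would go too far to say that practice will appear as a VR benefit, since no practice effect is given. It would also go too far to say that the trial's stereoacuity conclusion is compromised, since independent masked tests exist. The primary outcome, best corrected visual acuity measured by masked orthoptists, and the sample size are unaffected.

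**What to change.** Change the outcome wording in two places.

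1. Designate the Vivid Vision Home scores as exploratory or training-process measures. Keep collecting and reporting them in both periods, with a stated caveat that the VR period carries extra practice on the software. Restricting them to the VR period would discard planned data for no gain.
2. State that VR-versus-glasses conclusions on stereoacuity and binocular function rest on the tests outside the headset: Lang II, TNO, Titmus, Bagolini, prism-cover and red filter by masked orthoptists, with ASTEROID as support.

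This needs no new visits, tests or data. The cost is that vergence speed and range, which the listed out-of-headset tests do not measure, and suppression as measured by the virtual Worth 4 Dot, would have only exploratory evidence between treatments. Because suppression is named in the aims, that aim should say so.
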